### Sample Size

As previous RCTs have not investigated EA as a combination intervention in patients with ISSNHL with tinnitus, it is challenging to determine the optimal sample size through power calculation. Therefore, rather than performing a formal sample size estimation, this trial will adopt a preliminary exploratory clinical pilot design to estimate the appropriate sample size [28]. However, to preliminarily assess the feasibility of the proposed intervention, we will ensure an adequate number of participants in our experimental design by adhering to the established guideline of a minimum of 12 participants per group for pilot studies [29]. A previous study suggested that each group should have a sample size ranging from 20 to 25 cases for exploratory clinical trials assessing the effectiveness of intervention measures [30]. Therefore, in this study, each group will consist of 25 patients, resulting in a total of 50 cases across the 2 groups. To account for a potential dropout rate of 20%, we will recruit a total of 60 patients (30 per group). The results of this study will provide effect size data for calculating sample sizes in future large-scale RCTs.

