### Oversight and Monitoring

The principal investigators (JH and XH) will oversee the trial and report any serious adverse events to the Tongren Hospital Ethics Committee. Detailed records of adverse events—including their timing, severity, and treatment—will be maintained. In the event of an adverse reaction, a senior acupuncturist and otolaryngologist will evaluate whether the patient should be excluded from the study, and the clinical supervisor will be informed accordingly. Researchers will document the event details in the case report form (CRF; Multimedia Appendix 2) and ensure follow-up care until the patient stabilizes, with a summary report sent to the relevant authorities. Audiologists, acupuncturists, and nurses will conduct weekly follow-up calls to monitor symptoms and manage potential adverse reactions.

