### Statistical Analysis

All efficacy analyses will follow the intention-to-treat principle, including all randomized participants. Statistical analyses will be performed using SPSS version 22.0 (IBM Corp). Continuous variables, including PTA, THI, SAS, and SF-36, will be reported as means (SDs) for normally distributed data, or as medians (IQRs) for nonnormally distributed data. Tinnitus matching (frequency and loudness) will be treated as a categorical variable and summarized as proportions or percentages.

Baseline PTA distributions for both groups will be reported as means (SD) or medians (IQRs). Differences in baseline hearing loss severity will be assessed using the 2-tailed (unpaired) independent samples *t* test (for normally distributed data) or the Mann-Whitney *U* test (for nonnormally distributed data). If significant differences are identified, group comparisons will be adjusted for hearing loss severity using analysis of covariance to ensure comparability.

Changes in PTA, THI, SAS, and SF-36 across 6 time points (t0, t1, t2, t3, t4, and t5) will be evaluated using repeated measures analysis of variance for normally distributed data, or the Friedman test for nonnormally distributed data. Changes in tinnitus matching across the 6 time points will be assessed using the Cochran *Q* test to detect overall differences. If significant, pairwise comparisons will be conducted using the McNemar test with a Bonferroni correction for multiple comparisons.

Group differences in PTA, THI, SAS, and SF-36 at each time point will be analyzed using the independent samples *t* test (for normally distributed data) or the Mann-Whitney *U* test (for nonnormally distributed data). If baseline hearing loss severity differs significantly, analysis of covariance will be applied to adjust for this covariate. Differences in tinnitus matching at each time point will be evaluated using the chi-square test or Fisher exact test, as appropriate. Statistical significance will be set at α=.05 (2-sided).

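### The named longitudinal tests do not fit the promise to analyse all randomized participants, and no arm-by-time comparison is stated

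*Protocol article*

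**What the plan says.** All of this is in the protocol article. Statistical Analysis opens with the population: "All efficacy analyses will follow the intention-to-treat principle, including all randomized participants". It then separates two questions.

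- Change over time. For the four continuous measures (PTA, THI, SAS, SF-36), the course from t0 to t5 "will be evaluated using repeated measures analysis of variance for normally distributed data, or the Friedman test for nonnormally distributed data". The matching outcome has its own within-subject method, a *Q* test: "Changes in tinnitus matching across the 6 time points will be assessed using the Cochran".
- Difference between arms. The section states: "Group differences in PTA, THI, SAS, and SF-36 at each time point will be analyzed using the independent samples". That is a *t* test, replaced by Mann-Whitney *U* if nonnormal. Tinnitus matching gets a chi-square or Fisher test at each visit. Analysis of covariance enters only if baseline hearing loss differs significantly.

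The significance level is .05, two-sided. The only multiplicity correction is Bonferroni for the McNemar pairwise comparisons. Missing data appear only as a descriptive feasibility indicator. Sample Size raises 50 to 60 with the words "To account for a potential dropout rate of 20"%. Under Oversight and Monitoring, after an adverse reaction, senior clinicians "will evaluate whether the patient should be excluded from the study".

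**The concern.** The stated population and the stated tests do not match. A conventional repeated-measures ANOVA in SPSS, and the Friedman test, need a full row of visits for each participant. Someone who misses one of six visits leaves the analysis altogether, so the set analysed is defined by what happens after randomization. If the reasons for missing a visit differ between arms, the comparison loses the protection of randomization.

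The second problem is what these tests answer. Friedman asks whether one sample changes over time. The protocol's own Discussion cites about 56% recovery in patients seen within 7 days of onset, so change is expected in both arms and says nothing about EA. ANOVA could carry an arm factor, but none is written down. The between-arm question is left to a grid of single-visit tests with no visit or outcome put first.

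Sample Size says the effect sizes will be used to plan a larger trial, so a distorted or selectively read estimate would carry forward.

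**Working it through.** **Inputs.** 25 evaluable per arm, 50 in total; 20% dropout; 60 recruited, 30 per arm (Sample Size). Six time points, five after baseline; two-sided .05 (Statistical Analysis). Eight SF-36 dimensions and two parts of tinnitus matching (Outcome Measures).

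**The plan's own figure.** 50 × 1.20 = 60, which reproduces the stated total. (50 / 0.80 = 62.5, so 63 would be needed to keep 50 after 20% loss. That is a separate matter.)

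**Participants left in the longitudinal tests.**
- 60 × (1 − 0.20) = 48, or 24 per arm. This is the only count that rests on the document's figures alone.
- If there were instead no dropout, but visits were missed independently (assumed 2%, 5% or 10% at each follow-up visit), those with all visits would number 60 × 0.98^5 = 54, 60 × 0.95^5 = 46 or 60 × 0.90^5 = 35.
- At the same rates a single-visit test keeps 60 × 0.98 = 59, 60 × 0.95 = 57 or 60 × 0.90 = 54. The per-visit tests therefore lose far fewer people, though not the same people each time.
- Numerical check: a Friedman test on 60 rows, 12 of them lacking the last visit, gave the same result (statistic 1.952, p = 0.856) as on the 48 complete rows.

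**What Friedman detects.** Simulation with 30 per arm, six visits, 2,000 runs, assumed between- and within-subject SD of 1, both arms pooled:

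| Scenario | Friedman rejects | Mann-Whitney at t5 rejects |
|---|---|---|
| No change in either arm | 4.8% | 5.05% |
| Both arms improve equally | 100% | 4.8% |
| Only one arm improves | 90% | 97% |
| Arms move in opposite directions | 3% | 97% |

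Friedman follows the average change over both arms. It rejects always when the arms are identical and improving, and at about the null rate when they diverge symmetrically. Run within each arm it still gives no test between arms. Cochran *Q* is likewise a within-subject test on complete rows with no arm term.

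**Number of arm comparisons.** PTA, THI, SAS and eight SF-36 dimensions make 11 outcomes; 11 × 5 = 55. Two tinnitus items × 5 = 10. The total is 65, and 65 × 0.05 = 3.25 false positives are expected if there is no effect. The expected count does not require independent tests. It assumes one PTA summary per visit and a separate test for each SF-36 dimension. With SF-36 counted once, it is 4 × 5 + 10 = 30 tests and 30 × 0.05 = 1.5.

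**The case against.** The best defence is that the document never says complete cases. The named tests can include everyone if missing values are imputed, and an imputation rule commonly sits in an analysis plan or full protocol that is not shown. That stands. The absence of such a rule is not the finding, and the 48 is conditional on there being none. It does not answer the missing arm-by-time comparison, because the tests themselves are fixed here.

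Four stronger readings are tempting and are not supported.

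- A reader might infer that the per-visit *t* tests also use completers only. They use whoever has a value at that visit.
- A reader might infer that nonnormal outcomes get no arm comparison at all. That is true of Friedman, not of the plan, which gives them Mann-Whitney *U* at each visit. What is missing is the longitudinal comparison.
- A reader might take the adverse-reaction sentence as contradicting intention-to-treat. It does not say that follow-up stops or that data are removed. It is ambiguous, and the Statistical Analysis section governs the analysis set.
- The Results section reports 42 enrolled and 35 completed, 21 control and 14 EA. If all 42 are randomized, blocks of 4 in two centres limit the arm difference to 4. That implies 19 to 21 in EA, so 5 to 7 of the 7 non-completers are in that arm. This looks like loss in EA, but no dropouts are reported and some of the 7 may still be in treatment. Not yet completed is not lost.

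It is also fair that these are exploratory outcomes in a pilot without a formal power calculation, and that the feasibility outcomes are descriptive and untouched.

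**Conclusion.** The point holds in this form. Without imputation, the named longitudinal tests cannot deliver the promised population: at most 48 of 60 at the protocol's own dropout allowance. Whatever the missing data, Friedman cannot compare the arms over time, and no group or interaction term is stated for the ANOVA. The arm comparison then rests on about 65 unranked single-visit tests, with 3.25 false positives expected under no effect (30 tests and 1.5 if SF-36 is counted once).

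The 48 rests on the planned 20% occurring. Lower counts need assumed visit-level missingness. A probability of at least one false positive would need the tests to be independent, which repeated visits on the same patients are not, so none is claimed.

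This should be fixed rather than must be fixed. The outcomes are exploratory in a pilot, although the Abstract also calls PTA, tinnitus matching and THI primary, and Sample Size says the effect sizes will inform the next trial.

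**What to change.** For PTA, THI, SAS and SF-36, replace repeated-measures ANOVA and Friedman with one linear mixed model per outcome, available as MIXED in the SPSS already named. Include arm, categorical visit, arm-by-visit, baseline value and centre, with an unstructured covariance, and use every available visit.

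- Name one arm contrast in advance (one outcome at one visit, for example t2). Report the other visits and outcomes as estimates with 95% confidence intervals.
- A model with baseline only as a covariate still drops anyone with no post-baseline value. Either keep the baseline measurement in the outcome vector in place of the covariate, or use multiple imputation.
- For skewed scores use a transformation or bootstrap intervals.
- The model assumes data missing at random, so add one sensitivity analysis for departures from that, such as delta-adjusted multiple imputation.
- State under Oversight and Monitoring that a patient excluded after an adverse reaction stays in outcome follow-up and analysis unless consent is withdrawn, in line with Statistical Analysis. No view is taken on when treatment should stop.

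The linear model does not cover tinnitus matching, which is analysed as categories and needs its own longitudinal method.

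The cost is revised analysis wording, one clarified sentence, a little more programming, and continued visits for a few patients. The article places analysis after publication of the protocol, so this can be settled before unblinding.

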**Methods:**

In this double-center, assessor-blinded, randomized controlled trial, 60 patients with ISSNHL accompanied by tinnitus will be randomly allocated to either the EA group, receiving EA combined with medication, or the control group, receiving standard medication treatment, for a total treatment duration of 4 weeks. Follow-up assessments will be conducted at weeks 2 and 4, and at 1, 2, and 3 months after treatment. The feasibility primary outcomes are recruitment rate, adherence rate, data completeness, and safety outcomes. The primary outcome measures will include pure tone audiometry, tinnitus matching, and the Tinnitus Handicap Inventory, while the secondary outcome measures will comprise speech-recognition thresholds in noise, the Self-Rating Anxiety Scale, and the 36-item Short Form Health Survey Questionnaire.

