**Tinnitus frequency matching**
Tinnitus frequency matching is performed using an audiometer (Otometrics Conera). A pure tone with an intensity similar to the tinnitus sound is presented to the ear opposite to the tinnitus-impacted ear or the more severe side, with the frequency adjusted between 0.25 and 8 kHz. This adjustment continues until the presented pure tone frequency matches or closely resembles the patient’s perceived tinnitus frequency, which is then defined as the tinnitus pitch. For patients who cannot match a pure tone, a narrowband noise frequency is used, and the center frequency of this narrowband noise is defined as the tinnitus pitch. Tinnitus frequencies are categorized as low (<1 kHz), medium (1-4 kHz), and high (≥4 kHz).

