**Tinnitus loudness matching**
After determining the tinnitus pitch, the audiologist matches the loudness at this frequency. Starting from the hearing threshold at the tinnitus pitch, the intensity of the test tone is gradually increased in 1-dB increments until it just masks the tinnitus sound. The difference between the measured sound intensity and the corresponding hearing threshold at this frequency is recorded as the tinnitus loudness [37]. Tinnitus loudness is classified into 5 levels based on the World Health Organization hearing loss grading: ≤25 dB, 26-40 dB, 41-60 dB, 61-80 dB, and ≥81 dB [38].

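### The tests named for change over time in tinnitus matching are for binary data, but pitch has 3 classes and loudness 5, and no binary split is stated

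*Protocol article*

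**What the plan says.** The abstract counts tinnitus matching among the main efficacy measures: "The primary outcome measures will include pure tone audiometry, tinnitus matching, and the Tinnitus Handicap Inventory". The Methods section places the same three measures under the heading for exploratory primary outcomes, and Table 1 calls them exploratory.

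Textbox 1 defines the outcome in two parts.
- Pitch: "Tinnitus frequencies are categorized as low (<1 kHz), medium (1-4 kHz), and high (≥4 kHz").
- Loudness: "The difference between the measured sound intensity and the corresponding hearing threshold at this frequency is recorded as the tinnitus loudness". The tone is raised in 1-dB steps. Then: "Tinnitus loudness is classified into 5 levels based on the World Health Organization hearing loss grading", with limits ≤25, 26-40, 41-60, 61-80 and ≥81 dB.

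The Statistical Analysis section fixes the scale: "Tinnitus matching (frequency and loudness) will be treated as a categorical variable and summarized as proportions or percentages". It then names three procedures.
- Change over time: "Changes in tinnitus matching across the 6 time points will be assessed using the Cochran" Q test.
- If that is significant: "pairwise comparisons will be conducted using the McNemar test with a Bonferroni correction for multiple comparisons".
- Between arms: "Differences in tinnitus matching at each time point will be evaluated using the chi-square test or Fisher exact test, as appropriate".

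**The concern.** Cochran Q and McNemar are methods for a binary response, and the outcome they are assigned to has three or five classes. An analyst who follows the text must either compute a statistic that has no meaning on these data or choose a split that the article does not state. By the Results section, 35 of 42 enrolled participants had already completed posttreatment assessments, so a split chosen now could be influenced by the data.

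Cochran Q also has no term for treatment arm. It detects change over time, which recovery on medication alone can produce; the Discussion itself cites about 56% recovery among patients seen within 7 days of onset. The Sample Size section says the trial will supply effect sizes for later trials, and a within-patient time trend gives no such effect for tinnitus matching.

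The class definitions have faults of their own. One pitch value has two classes. Loudness is a level above threshold, but it is cut at limits taken from a grading of hearing loss, which is a different quantity.

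**Working it through.** The plan gives no figure to reproduce here. The check is whether each named test accepts the outcome as defined.

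**Inputs.** Pitch has 3 classes and loudness 5 (Textbox 1). There are 6 time points, t0 to t5, and two-sided α is 0.05 (Statistical Analysis). The illustration uses 25 patients, the analysable number per group in Sample Size.

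**Cochran Q.** With k time points, column totals G and patient totals L,

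Q = (k−1)[k·ΣG² − (ΣG)²] / [k·ΣL − ΣL²].

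The denominator equals ΣL(k−L). With 0/1 data and k = 6, L lies between 0 and 6, so no patient's term is negative. With class codes this fails:
- Pitch coded 0-2, highest class at all six visits: L = 12, and the term is 12 × (6−12) = −72.
- Loudness coded 0-4, highest class at all six visits: L = 24, and the term is 24 × (6−24) = −432.

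Simulated data with no change over time (n = 25, k = 6, 4,000 runs each, classes equally likely) gave:

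| Classes | Denominator zero or negative | Q above the 5% critical value (5 df) |
|---|---|---|
| 2 | 0% | 4.5% |
| 3 | 95.25% | 4.675% |
| 5 | 100% | 0% |

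The 4.675% in the 3-class row is not evidence that the test works. It is 187 of 4,000 runs, and only 190 runs had a positive denominator (4,000 × 0.0475), so nearly every run with a positive denominator rejected. In one 3-class data set, coding the classes as 1-2-3, 0-1-2 or 2-1-3 gave Q = −1.96, −29.1 and −0.61. The value depends on arbitrary labels.

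**McNemar.** Two visits cross-classified give a 3×3 table for pitch and a 5×5 table for loudness, not 2×2. The Bowker extension accepts such tables (3×2/2 = 3 df for pitch, 5×4/2 = 10 df for loudness), but the article does not name it.

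**If a binary split were added.** There are 2 ordered cut-points for pitch and 4 for loudness. Six time points give 6×5/2 = 15 pairs, so the Bonferroni level is 0.05/15 = 0.0033. An exact McNemar test with m discordant pairs, all in one direction, has p = 2 × 0.5^m. For m = 9, p = 0.0039; for m = 10, p = 0.00195. At least 10 discordant patients are needed, which is 10/25 = 40% of one arm if the test is run within an arm.

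**Between-arm tests.** Chi-square and Fisher tests accept 2×3 and 2×5 tables, so these can be run. They compare the distribution of classes at one visit; they do not use the patient's baseline class and ignore the order of the classes.

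**Class limits.** A match at exactly 4 kHz, inside the 0.25-8 kHz test range, meets both the medium and the high definition. A fall from 24 to 4 dB is 20 test steps and stays within ≤25 dB. A fall from 26 to 25 dB is one step and changes class.

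**The case against.** The strongest reply is that the treatment comparison does not depend on Cochran Q. The arms are compared by chi-square or Fisher tests on the classes as defined, and those tests are valid on 3 or 5 levels. Because Cochran Q has no arm factor, even a late choice of split for it could not bias that comparison, and the article keeps statisticians blinded until the analysis is complete. A split could also be fixed in an analysis plan that is not shown. McNemar has an established extension to larger tables. The outcome is exploratory, the trial is a pilot without a power calculation, and the feasibility outcomes are descriptive.

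Most of this stands, and it limits the point to the analysis of change over time. It does not remove it. The article does not merely leave a detail open: it names tests that conflict with its own definition of the outcome. Bowker replaces the pairwise step only, not the overall test that triggers it.

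A reader might also infer that the upper loudness classes would be almost empty, or that binning loses most of the measured change. The documents support neither. They give no output limit for the audiometer and no distribution of loudness, and they do not say which ear is used for loudness matching. The pitch tone goes to the ear opposite the affected or worse one, where thresholds may be low. The 24-to-4 dB example shows that a large change can be missed, not how often that happens.

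**Conclusion.** The point holds for the stated analysis of change over time. Cochran Q cannot be applied meaningfully to a 3-class or 5-class outcome, the standard McNemar test does not fit the resulting tables, and no binary split is given. It would be wrong to conclude that tinnitus matching cannot be analysed at all, or that the arms are never compared on it. The accurate statement is narrower: the arms are compared on levels at each visit, and no stated test for this outcome compares change between them. The overlap at 4 kHz and the mismatch between the loudness scale and its cut-points follow directly from Textbox 1.

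This should be fixed before the analysis begins. It is not critical, because it affects one exploratory primary outcome of a pilot. The Q-formula argument rests on arithmetic alone; the simulated percentages also assume equally likely classes and independent visits, and serve only as illustration.

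**What to change.** Replace Cochran Q and McNemar for this outcome.

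- **Loudness:** analyse the recorded dB value with a repeated-measures model containing arm, visit, arm-by-visit and baseline loudness. At minimum, apply the methods the article already states for THI: repeated measures ANOVA or Friedman over time, and the t test or Mann-Whitney test between arms. That minimum gives no baseline-adjusted comparison of change, so the model is preferable. Keep the 5 classes for description only.
- **Pitch:** analyse the class with an ordinal or multinomial repeated-measures model (GEE or mixed) containing arm, visit and arm-by-visit. Define medium as 1 to <4 kHz so that each match has one class.

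A smaller repair is to state one binary split for each part now and keep the named tests. That makes them runnable, but it leaves the 15-pair correction and still offers no comparison of change between arms.

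The cost is a revision of the analysis wording and a documented change of the loudness scale from categorical to continuous. The dB value is already recorded, so no new measurements, visits or patients are needed. The article places analysis after publication of the protocol, so the change can be dated before it.

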## Methods

### Design and Setting

The study is designed as a prospective, single-blinded RCT. It will take place in the clinics of Beijing Tongren Hospital, Capital Medical University, and the Acupuncture and Moxibustion Hospital, China Academy of Chinese Medical Sciences (CACMS). Eligible participants will be randomized in a 1:1 ratio to either the EA group (EA plus medication) or the control group (standard medication alone). This pilot trial will apply a longitudinal follow-up design, with a baseline assessment before enrollment (t–1), allocation and intervention initiation at t0, on-treatment follow-ups at week 2 (t1), week 4 (t2), and posttreatment follow-ups at 1 month (t3), 2 months (t4), and 3 months (t5) after intervention completion, barring loss to follow-up. This trial will be reported in accordance with the CONSORT (Consolidated Standards of Reporting Trials)-EHEALTH (see Multimedia Appendix 1) statement, which defines standard reporting items for RCTs [27]. Participant recruitment began on July 15, 2024, with the study scheduled to continue until December 2025. The flowchart is illustrated in Figure 1, and the overall procedure is presented in Table 1.

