	**Exploratory outcomes**																		
			Pure tone audiometry	N/A		✓		✓		✓		✓		✓		✓			
			Tinnitus matching	N/A		✓		✓		✓		✓		✓		✓			
			Tinnitus Handicap Inventory	N/A		✓		✓		✓		✓		✓		✓			

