### Enrollment, Randomization, and Blinding

Recruitment will be conducted through WeChat (Tencent Holdings Limited) public account notifications, roll-up banners at clinic entrances, and collaboration with community committees for promotion.

Stratified block randomization will be performed according to the study center. Both groups will be assigned in a 1:1 ratio to the EA and control groups using a block size of 4. [name], a statistician from the Evidence-Based Medicine Center at CACMS, will serve as the randomization coordinator and will be responsible for generating the stratified block randomization sequence using SAS 9.3 software (SAS Institute). She will not participate in the trial’s implementation or data analysis. After obtaining informed consent and before initiating treatment, the treating physician at each center will contact the randomization coordinator by phone to receive the randomization number and group assignment.

Because of the nature of acupuncture, it is not possible to blind the acupuncturists or participants. However, steps will be taken to minimize bias from single blinding as much as possible. Acupuncturists will receive specialized training before participating in the study and will be instructed not to discuss treatment procedures or outcomes. They will also be excluded from evaluating the results. Patients will be treated separately to prevent contact between participants. The randomization staff and acupuncturists will have access to the assignment information, but the outcome evaluators and statisticians will remain blinded throughout the entire clinical trial. Statisticians will speculate on the group allocation before data analysis to assess the efficacy of blinding, and unblinding will only occur after the completion of data analysis.

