Most studies currently agree that the earlier patients with ISSNHL receive treatment, the better their prognosis. The study by Byl [57] indicated that patients who received medical attention within 7 days of onset had an approximately 56% recovery rate, whereas those who presented after 30 days had a recovery rate of only 27% (also see [58]). The study by Diao et al [59] also demonstrated that the number of days from onset to treatment was an independent prognostic factor, with shorter time intervals correlating with better outcomes. Therefore, all patients selected for this study were within 7 days of onset. The medication treatment protocol for ISSNHL with tinnitus is the same as that for ISSNHL. The inclusion of multiple variables (ie, multiple drugs) in the standard treatment is driven by the complex pathophysiology of ISSNHL. Research indicates that inflammation is likely a key contributing factor, and corticosteroids such as prednisone are used to reduce inner ear inflammation and edema, thereby improving hearing outcomes [60]. Ginkgo biloba extract, known for its circulation-enhancing and antioxidant properties, may help restore cochlear microcirculation [61]. Batroxobin, a snake venom–derived enzyme with fibrinolytic activity, may improve inner ear blood flow by reducing blood viscosity [62]. This combination of drugs is designed to simultaneously target distinct pathological mechanisms, thereby enhancing overall therapeutic efficacy. The rationale for this combined approach is supported by evidence from studies conducted in China. A retrospective study involving 342 patients with total deafness-type ISSNHL found that adding batroxobin to a treatment regimen of Ginaton and glucocorticoids significantly improved hearing recovery outcomes and maintained plasma fibrinogen levels within a safe and prognostically favorable range [63]. This improvement was particularly notable in terms of hemorheological parameters and peripheral blood T-cell subset reactivity. Additionally, a 2023 meta-analysis further corroborated the efficacy of Ginkgo biloba extract as an adjuvant therapy, suggesting it may outperform corticosteroid monotherapy [64]. These findings support the decision to incorporate multiple pharmacological agents into the standard treatment protocol, aligning with the goal of addressing the multifaceted nature of ISSNHL.

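### Covariate adjustment hangs on a significance test of baseline PTA, never uses baseline THI, SAS or SF-36 for those outcomes, and leaves out the stratifying centre, so precision is lost

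*Protocol article*

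**What the plan says.** The Statistical Analysis section first sets a baseline comparison: "Differences in baseline hearing loss severity will be assessed using the 2-tailed (unpaired) independent samples" t test, or by the Mann-Whitney test if the data are not normal. It then makes adjustment depend on the result: "If significant differences are identified, group comparisons will be adjusted for hearing loss severity using analysis of covariance to ensure comparability". For the between-arm analysis the default is unadjusted: "Group differences in PTA, THI, SAS, and SF-36 at each time point will be analyzed using the independent samples" t test, again with Mann-Whitney as the alternative. The condition is then repeated: "If baseline hearing loss severity differs significantly, analysis of covariance will be applied to adjust for this covariate".

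Hearing loss severity is the only covariate named. The t0 values of PTA, THI, SAS and SF-36 also enter the repeated measures ANOVA or Friedman test, but as one of six time points, not as a covariate.

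Under Enrollment, Randomization, and Blinding: "Stratified block randomization will be performed according to the study center". The Statistical Analysis section does not mention centre.

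On the timing of baseline, Design and Setting describes a design "with a baseline assessment before enrollment (t–1), allocation and intervention initiation at t0". Table 1 marks PTA and every other exploratory and secondary outcome as not applicable at t-1 and ticks it at t0, the column that also holds allocation.

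**The concern.** In a properly randomized trial a baseline difference is due to chance, so a significance test of it answers no useful question. Whether a covariate is worth adjusting for depends on how strongly it predicts the outcome and on how large the observed gap is, not on whether the gap reaches p<0.05. In a small trial a sizeable gap can fall short of significance and stay in the estimate.

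The rule also looks at one variable only. A chance imbalance in baseline THI is not addressed even if the trigger fires, because the covariate would then be hearing severity.

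At stake is the precision of the effect estimates. The Sample Size section says they will be used to size future large trials, so noise or chance imbalance left in them is carried forward.

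**Working it through.** **Inputs from the protocol article.** Two-sided alpha 0.05; 1:1 allocation; 30 per arm recruited; 25 per arm intended as evaluable; 20% dropout. The stated 60 is reproduced by 50 × 1.20 = 60. Losing 20% of 30 leaves 30 × 0.80 = 24 per arm, so 24 and 25 are both used below.

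**Assumed, because the documents give no value.** Baseline-outcome correlation ρ = 0.3, 0.5, 0.7; effect 0.6 SD (also 0.8 SD).

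**1. How often the trigger fires.** Randomization makes the null hypothesis of the baseline test true, so it is significant in about 5% of trials. About 95% are analysed unadjusted.

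**2. Largest gap left unadjusted.** Threshold = t(0.975, 2n−2) × √(2/n), in SD units.
- n = 24: 2.013 × 0.2887 = 0.58
- n = 25: 2.011 × 0.2828 = 0.57
- n = 30: 2.002 × 0.2582 = 0.52

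**3. Error given an unadjusted gap.** Shift = ρ × gap. For a 0.5 SD gap this is 0.15/0.25/0.35 SD at ρ = 0.3/0.5/0.7.

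**4. Precision given up.** ANCOVA multiplies the variance by 1 − ρ² = 0.91/0.75/0.51. That is worth 1.10/1.33/1.96 times the sample size.

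**5. Simulation of the rule** (t test unless baseline p<0.05, otherwise ANCOVA) against ANCOVA always:

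| Quantity | ρ=0.3 | ρ=0.5 | ρ=0.7 |
|---|---|---|---|
| Power, 24 per arm, 0.6 SD: rule | 52% | 53% | 54% |
| Power, same: ANCOVA always | 55% | 64% | 81% |
| Power, 25 per arm, 0.8 SD: rule | 80% | 80% | 81% |
| Power, same: ANCOVA always | 82% | 89% | 97% |
| SD of estimate, 25 per arm: rule | 0.280 | 0.274 | 0.265 |
| SD of estimate, same: ANCOVA always | 0.272 | 0.247 | 0.205 |
| Type I error, 25 per arm: rule | 4.8% | 4.4% | 3.7% |
| Mean error given a 0.40-0.55 SD gap, 24 per arm: rule | 0.13 | 0.22 | 0.30 |

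The 0.40-0.55 SD window holds about 11% of trials, and with ANCOVA always the mean error there is about zero. Repeat runs of the power figures differ by one or two percentage points. At 24 per arm the rule's mean estimate over all randomizations was 0.599-0.603 for a true 0.6.

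**6. THI, SAS and SF-36.** The simulation uses the outcome's own baseline as both trigger and covariate, so it describes PTA. For the questionnaires the rule never supplies the own baseline. If baseline PTA says little about them, the SD of the estimate stays near √(2/25) = 0.283 at 25 per arm, against 0.272/0.247/0.205 with own-baseline ANCOVA.

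**7. Centre.** No centre effect is given, so the gain from including it cannot be computed.

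**The case against.** This is a pilot. Its feasibility outcomes are descriptive, efficacy is exploratory and there is no power calculation, so no confirmatory claim depends on the rule. The effect size and correlations above are assumed, and at ρ = 0.3 the gain is small. All of this stands, and it limits how serious the point is.

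Centre could be left to an analysis plan that is not shown. That would answer a plan that was silent on covariates. This one fixes when to adjust and for what, so always adding own baseline and centre improves a stated rule.

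Several stronger readings are tempting, and the documents do not support them:
- **The rule biases the trial or inflates false positives.** Over all randomizations the estimate is unbiased and the test is mildly conservative. The error is conditional on the gap that happens to occur.
- **No outcome is ever adjusted for its own baseline.** For PTA the triggered covariate is its own baseline, though only in about 5% of trials. The statement is true for THI, SAS and SF-36.
- **The baseline test has low power to detect a real gap.** Randomization excludes a true population gap, so power against one is not the relevant quantity.
- **Self-rated THI is recorded after patients know their arm.** Table 1 shows allocation and outcomes in the same column but gives no order within the visit, and no section says THI follows allocation. The text and the table do conflict, but that is a separate matter from covariate choice.

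Time from onset is sometimes proposed as a further covariate, since the Discussion cites evidence that "the number of days from onset to treatment was an independent prognostic factor". Eligibility already restricts onset to one week, while the recovery rates quoted there contrast 7 days with more than 30. Its value within that week is unknown, so it is optional.

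**Conclusion.** The point holds as a loss of precision, with error conditional on an unflagged imbalance. About 95% of trials run under this rule would be analysed unadjusted, and at 24-25 per arm an observed PTA gap of up to about 0.57-0.58 SD would stay in the estimate. At moderate to high assumed correlations (0.5-0.7) the cost is roughly 11 to 27 power points for a 0.6 SD effect at 24 per arm (64 − 53 and 81 − 54). At 0.3 it is about 3 points (55 − 52). These sizes rest on assumed correlations and effects and on normally distributed outcomes.

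The validity of the randomized comparison is not in question. The change is worth making because the estimates will feed later sample size calculations and the improvement is nearly free. The conflict over baseline timing is real and needs reconciling, but the documents do not show that any baseline measure was affected by knowledge of allocation.

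**What to change.** In Statistical Analysis, delete the significance test of baseline hearing loss and both conditional sentences; still report baseline PTA by arm descriptively. State that PTA, THI, SAS and SF-36 will each be compared by ANCOVA, or by a mixed model over the follow-up visits, with the outcome's own baseline value and centre as covariates whatever the baseline difference. Say in advance what replaces this if an outcome is badly skewed, since the Mann-Whitney test cannot carry covariates. Tinnitus matching is analysed as categorical and is outside this change.

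The cost is about 2 degrees of freedom and a few sentences. Baseline measures are already scheduled and centre is known for every participant. The article says the analysis is still to come, so the change can be fixed before it starts.

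Separately, make Design and Setting and Table 1 agree on the baseline time point, and state whether baseline measures precede allocation. With 42 participants already enrolled, that statement must describe what was actually done for them, so it needs a check of the records and not only new wording.
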